#### Self-reported outcomes

The self-reported measures of potential harms and benefits of BC-Predict to be completed by a sub-sample of participants are shown in Table 1.

**Table 1 Tab1:** Self-reported measures to be assessed, at each of the three timepoints.

Baseline	3 months	6 months
State Anxiety [29]	State Anxiety [29]	State Anxiety [29]
Cancer Worry [30]	Cancer Worry [30]	Cancer Worry [30]
Risk perceptions [31]	Risk perceptions [31]	Risk perceptions [31]
Attitudes to screening [32]		Attitudes to screening [32]
Knowledge [33]		Knowledge [33]
Intention (future screening) [32]	Intention (future screening) [32]	Intention (future screening) [32]
Health status (EQ-5D5L) [34]	Health status (EQ-5D5L) [34]	Health status (EQ-5D5L) [34]
Capability [35]	Capability [35]	Capability [35]
	Satisfaction with information [36]	Satisfaction with information [36]

**Informed choices regarding screening will be estimated from attitudes to screening at baseline, knowledge and screening attendance, using a standard approach* [17]

***Women invited to BC-Predict will receive the above. Women invited to NHS-BSP will receive the above minus the satisfaction with information questionnaire*

### Analysis plan and power calculations

#### Core outcomes

In total, approximately *n* = 18,700 women will be offered BC-Predict and *n* = 18,700 will be offered usual care NHSBSP over the total 16-month period. Based on the recruitment rate in PROCAS, *n* = 18,700 women being offered BC-Predict should result in 8000 women taking it up. The attendance rate to usual NHSBSP in Greater Manchester is 69% [5, 10].

Core outcomes will be compared for cohorts of women who are invited to BC-Predict and those who are invited to usual care (NHSBSP). Thus we will have in excess of 8000 participants in BC-Predict and NHSBSP groups for both comparisons: (a) within-site and (b) between sites over the same time period. The primary outcomes are binary. Logistic regression will be the primary statistical analysis method. We shall assess heterogeneity effects using interaction tests in the logistic regression, to examine differences in outcomes by time or location or screening type (prevalent v incident). Even in the presence of geographic or temporal heterogeneity of the effect, or of carryover effects continuing beyond the crossover period, we will still have sufficient data for a valid and fully powered comparison.

For core outcomes 1 and 2, we are interested in equivalence, in that we anticipate that invitation to BC-Predict will not substantially affect screening attendance. With 18,700 women in each group we will have in excess of 90% power to establish equivalence, defined as a 95%CI on the difference which does not exceed ±5% on the attendance rate at first offered appointment, if the latter is around 50% [37]. Similarly, we will have more than 90% power for the same comparison for eventual attendance within 180 days if the latter is around 70%.

Arguably, the most difficult to collect core outcome is 9, the proportion taking up chemoprevention. On the basis of PROCAS results we would anticipate that 1169 of the 8000 who consent to BC-Predict would have sufficient risk to be considered for chemoprevention and that 10% of these would take it up [8, 38, 39]. Thus 117 of the 8000 women (1.5%) receiving the intervention might be expected to be prescribed chemoprevention. It is anticipated that very few in the 18,700 sent the standard screening invitation would be prescribed chemoprevention, but even if as many as 0.9% did so, we would have 90% power to detect this as significant at 5% level with two-sided testing, and 80% power if 10% took up chemoprevention. The Greater Manchester Medicines Management group has agreed a shared care protocol stating that the initial prescription of tamoxifen and anastrozole should be made by a FHRP specialist. As such data from even those in the control arm should be available from prescriptions made in the FHRP clinics.

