## Methods/design

### Study design

A non-randomised fully counterbalanced study design will be used, to include equal numbers of participants from all sites who will be offered NHSBSP and BC-Predict. Specifically, in the initial 8-month time period, four screening sites will offer women eligible for breast screening BC-Predict. Three screening sites will offer women usual care NHSBSP. In the following 8-month time period the study sites switch to offer the other intervention (NHSBSP rather than BC-Predict; and vice versa). This ‘counter-balanced’ design will allow estimates of effect to be obtained from both within-sample and between-sample analyses.

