### Setting

Women will be recruited from seven sites within three NHS Breast screening programmes: three sites within the Greater Manchester programme (Withington Community Hospital, Oldham lntegrated Care Centre and the Trafford mobile screening van only), and two sites each based in the East Cheshire (Macclesfield District General Hospital and Stockport mobile breast screening van locations) and East Lancashire (Burnley General Hospital and East Lancashire mobile breast screening van locations) programmes. Women invited to screening in East Cheshire and Withington/Trafford in the first 8 months of the study will be offered BC-Predict and women in East Lancashire and Oldham offered screening as usual. After 8 months, BC-Predict will be offered to women in East Lancashire and Oldham, with women in Cheshire and Withington/Trafford offered screening as usual.

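### With one switch and two site groups, the planned interaction test by period cannot be separated from the site-group difference, nor the site-group part of the location test from the change between periods

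*Protocol article*

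**What the plan says.** The article's Study design section describes the layout: "A non-randomised fully counterbalanced study design will be used, to include equal numbers of participants from all sites", with a single exchange of arms, "In the following 8-month time period the study sites switch to offer the other intervention". The Setting section names the groups. On the first group: "Women invited to screening in East Cheshire and Withington/Trafford in the first 8 months of the study will be offered BC-Predict". On the reversal: "After 8 months, BC-Predict will be offered to women in East Lancashire and Oldham, with women in Cheshire and Withington/Trafford offered screening as usual". Group A is therefore four sites (two in East Cheshire, plus Withington and Trafford), with BC-Predict first. Group B is three sites (two in East Lancashire, plus Oldham), with BC-Predict second.

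On analysis, the Core outcomes part of the analysis plan says "Logistic regression will be the primary statistical analysis method" and then "We shall assess heterogeneity effects using interaction tests in the logistic regression, to examine differences in outcomes by time or location or screening type". It does not list the other model terms. It also does not say whether time means the two periods or calendar time, or whether location means site, programme or site group. The next sentence gives an assurance: even if the effect varies by place or time, or carries over past the switch, the data will still allow a valid comparison with full power.

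**The concern.** The interaction tests are the formal check the article names for whether the effect of offering BC-Predict varies by time or place. The sites were not randomised, so the two groups may differ at baseline for reasons unrelated to BC-Predict, and attendance may change between the two periods. If the tests measure those differences, the study may report an effect that changes when it is constant, or miss one that does change. Findings on where and when the offer works are meant to inform roll-out and a definitive study.

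A real change in the offer is also planned. Sub-study three adds information about delayed screening to the invitation in East Lancashire and Oldham in the last 4 of the 16 months. That falls in one site group and one period only, where a period-level test cannot separate it from a site-group difference.

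**Working it through.** **Inputs.** From the article: one switch, two 8-month periods, groups of four and three sites, 18,700 women per arm, attendance near 50% (first appointment) and 69–70% (overall or within 180 days), equivalence margin ±5 points. Assumptions, because the article gives no figure: 9,350 women per group-by-period cell (18,700 / 2), split equally among the sites of a group; independent women; two-sided 5% for the interaction tests; site-group gaps and drifts of 1 to 2 points.

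**The plan's own figure.** Equivalence power = 2Φ(0.05/SE − 1.96) − 1, with SE = √(2p(1−p)/18,700).
- p = 0.50: SE = 0.00517, and 0.05/0.00517 − 1.96 = 7.71.
- p = 0.70: SE = 0.00474, and 0.05/0.00474 − 1.96 = 8.59.

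Power exceeds 99.9% in both cases, so the stated figure of over 90% is reproduced. The problem is not sample size.

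**Algebra, log-odds scale.** Cells: A1 (BC-Predict), A2 (usual care), B1 (usual care), B2 (BC-Predict).
- Effect in period 1 minus effect in period 2 = (A1 − B1) − (B2 − A2) = (A1 + A2) − (B1 + B2). This is the site-group contrast.
- Effect in A minus effect in B = (A1 − A2) − (B2 − B1) = (A1 + B1) − (A2 + B2). This is the period contrast.

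**Design-matrix ranks over the 14 site-by-period cells.**

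| Model | Rank |
|---|---|
| site + period + arm | 9 |
| add arm × period | 9 (not estimable) |
| add arm × site group | 9 (not estimable) |
| site + period + arm × site | 14 (5 df beyond main effects) |
| site + arm, no period | 8 |
| site + arm × site, no period | 14 (6 df, one of which is the period contrast) |

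**Period test without site terms, true effect zero.** The contrast is twice the site-group log odds ratio. With cells at 0.69 and 0.70 it is 2 × 0.0472 = 0.0944. Its standard error is √[2/(9,350 × 0.69 × 0.31) + 2/(9,350 × 0.70 × 0.30)] = 0.0449, so z = 2.10 and the rejection rate is Φ(2.10 − 1.96) ≈ 56%.
- Gap of 2 points (0.69 and 0.71): z = 0.1905/0.0452 = 4.22, 99%.
- Near 50%, gap of 1 point: z = 0.0800/0.0414 = 1.93, 49%. Gap of 2 points: z = 0.1601/0.0414 = 3.87, 97%.

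**Masking.** Let BC-Predict lower attendance by 4 points in period 2 only.
- Equal groups (0.70, 0.70, 0.70, 0.66 for A1, A2, B1, B2): z = 0.1840/0.0448 = 4.11, detected about 98% of the time.
- Group A 2 points lower (0.68, 0.68, 0.70, 0.66): contrast −0.0030, z = −0.07, rejection 5%.

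**Site test (6 df) without a period term, true effect zero.** Noncentrality comes from the expected-count logistic fit.

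| Base rate | Drift | Noncentrality | Rejection |
|---|---|---|---|
| 50% | 1 point | 3.74 | 25% |
| 50% | 2 points | 14.97 | 84% |
| 69% | 1 point | 4.41 | 30% |
| 69% | 2 points | 17.81 | 91% |

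With period in the model, the remaining 5-df test has noncentrality 0 and keeps its nominal size.

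**What the pooled estimate assumes.** The group- and period-adjusted effect is [(A1 − A2) + (B2 − B1)]/2. Group and period differences cancel. If group B's period change exceeds group A's by δ, the estimate is off by δ/2. If carryover λ raises A2, it is off by −λ/2. The four cell means are used up by mean, group, period and arm, so the two-period data cannot check either term.

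**The case against.** A reader might infer that heterogeneity will be declared although the effect is constant. The document does not support that. A false positive needs site terms (for the period test) or a period term (for the location test) to be left out, and the article lists no terms. It also needs a real gap or drift, and the article reports none. With site terms, the two-period test drops out rather than misfiring.

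A reader might also infer that location effects can be compared only among sites of the same sequence. That goes too far. Greater Manchester contains both sequences, and site + period + arm + arm × programme has 11 columns and rank 11. East Cheshire can therefore be compared with East Lancashire if the period change is common and the effect is common within Greater Manchester. Nor is all testing by time lost: with site and calendar-month effects, a linear arm × month term is estimable (24 columns, rank 24). The screening-type interaction is unaffected.

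The article also plans both within-site and between-site comparisons. With zero effect, a gap d and no drift, the between-site contrasts would be +d and −d and the within-site contrasts zero, a pattern an alert analyst would recognise. That is fair, but it is a plausibility judgement on the same four cells. Once gap, drift and effect are mixed, no clean pattern remains.

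Model terms can properly be left to an analysis plan. No choice of site-level terms over these two periods, however, makes the period interaction identifiable, so the limit comes from the design and not from condensed reporting.

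**Conclusion.** The point holds in a bounded form. At the level of the two periods, the test by time either measures the baseline difference between non-randomised site groups or is not estimable. One of the six degrees of freedom of the site interaction is the period change. The identities follow from the stated layout alone. The rejection rates (49–56% and 97–99% for the period test, 25–30% and 84–91% for the site test) rest on assumed gaps or drifts of 1 and 2 points, 9,350 independent women per cell and the omission of the relevant main effects.

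The pooled effect with site and period terms is estimable, but only under a common period change across site groups and no carryover. These tests cannot establish either condition, so the assurance of validity under heterogeneity or carryover is stronger than the design allows. The amendment should be made, because it changes which conclusions about time and place the study can draw.

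**What to change.** In the Core outcomes part of the analysis plan:

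1. Fit arm with site and period fixed effects.
2. Drop the two-period arm × period and arm × site-group tests, or state that they are not identified in this design.
3. Test location heterogeneity with site and period in the model: 5 df at site level, assuming a common period change. Arm × programme may be added, stating that it assumes a common effect within Greater Manchester.
4. Test time heterogeneity only as change over calendar time within periods, for example a linear arm × month term with site and month effects, and say that it rests on that functional form.
5. Qualify the assurance of a valid, fully powered comparison: it assumes a common period change across site groups, which carryover would break.

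Optionally, request aggregate totals per site for a pre-study period of usual care. This depends on data permissions, since the posters that let usual-care women opt out would not have reached those women. It would make arm × period estimable with site terms, but would still not separate time, site-group and carryover explanations.

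The cost is wording, plus giving up separate claims about heterogeneity by period and by site group.

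### Core-outcome power and analysis treat women as independent although the offer is assigned by site and period, and the unconditional validity and power claim fails under carryover

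*Protocol article*

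**What the plan says.** Under Study design, assignment is non-randomised and by site: "in the initial 8-month time period, four screening sites will offer women eligible for breast screening BC-Predict", the other three offer usual care, and the sites then switch. Under Setting, "Women will be recruited from seven sites within three NHS Breast screening programmes". East Cheshire and Withington/Trafford start with BC-Predict; East Lancashire and Oldham start with usual care.

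The Core outcomes part of the analysis plan states: "Logistic regression will be the primary statistical analysis method". Time, location and screening type enter through interaction tests. For attendance, "With 18,700 women in each group we will have in excess of 90% power to establish equivalence", with equivalence "defined as a 95%CI on the difference which does not exceed ±5% on the attendance rate at first offered appointment". The assumed rates are about 50% at the first offered appointment and about 70% within 180 days. For chemoprevention, 90% power is claimed for 117 of 8,000 women (1.5%) against 0.9% in controls.

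The same section says that with geographic or temporal heterogeneity of the effect, or with carryover, "we will still have sufficient data for a valid and fully powered comparison". No intracluster correlation, design effect, site-period term or robust variance appears for the core outcomes. Hierarchical models are named only for the repeated questionnaire responses.

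**The concern.** The units that receive one offer or the other are 14 site-periods (7 sites × 2 periods), not 37,400 women. Attendance at a site can move between two 8-month periods for reasons unrelated to BC-Predict. A model that counts only binomial noise among women leaves that movement out of its intervals, and testing whether the effect differs by site or time does not put it back.

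The protocol itself contains sources of such movement. In the last four months, women in East Lancashire and Oldham also get information on delayed screening with their invitation (sub-study three). Refinements to procedures that may affect uptake are expected (Core outcomes, under Measures). Women aged 57 to 63 are eligible only at East Cheshire and East Lancashire, so screening type is tied to site.

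At stake is the attendance conclusion: ordinary drift could be reported as harm to attendance, or an interval that is too narrow could be read as proof of equivalence.

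**Working it through.** **1. The plan's own figures.** Inputs: 18,700 per group, margin 5 points, two-sided 95% CI, true difference zero.
- At 50% attendance: SE = √(2 × 0.25 / 18,700) = 0.52 points; half-width 1.96 × 0.517 = 1.01 points; power = 2Φ(5/0.517 − 1.96) − 1, above 99.9%. At 70% the SE is 0.47 points and power is again above 99.9%.
- About 2,600 women per group would give 90% at 50% attendance. The claim of more than 90% therefore reproduces, with a large reserve, if women are independent.
- Chemoprevention, 117/8,000 = 1.46% v 0.9%, two-sided 5%: 8,000 v 8,000 gives 90.9%, matching the stated 90%; 8,000 v 18,700 gives 97.4%. Neither includes clustering.

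**2. Adding site-by-period variation, both periods.** Assume equal cells of 37,400/14 = 2,671 women and a site-period SD of s. Cell variance is 0.25/2,671 + s². With sequences of 4 and 3 sites, the within-site estimate adjusted for period has variance ¼ × (1/4 + 1/3) × 2 × cell variance = (7/24) × cell variance. For s = 2 points: (7/24) × (0.0000936 + 0.0004) = 0.000144, so SE = 1.20 points, and 1.20/0.517 = 2.3. Residual df are 14 − 1 − 6 − 1 − 1 = 5 after the intercept, sites, period and treatment. The last three columns were simulated.

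| Assumed SD (points) | True SE (points) | Ratio to naive SE | Mean 95% half-width, t(5) | Equivalence power, t(5) | Type I error of naive test of a difference |
|---|---|---|---|---|---|
| 1 | 0.75 | 1.5 | 1.8 | above 99% | 18% |
| 2 | 1.20 | 2.3 | 2.9 | 82% | 40% |
| 3 | 1.70 | 3.3 | 4.2 | 40% | 55% |
| 4 | 2.22 | 4.3 | 5.4 | 16% | 65% |

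With a normal reference and known variance, power at 2 and 3 points is about 97% and 67%. At 70% attendance the t(5) powers are much the same, 84% and 41%.

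**3. Carryover.** Contamination would fall on period 2 in the sites that began with BC-Predict. Two contrasts remain:
- Period 1, four chosen sites against three others: arm cannot be separated from site.
- Period 1 against period 2 in East Lancashire and Oldham, which had usual care first: arm cannot be separated from time.

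Even if site differences in period 1 are treated as pure noise, equivalence power at 50% attendance is about 92%, 41%, 11% and 1% for between-site SDs of 1, 2, 3 and 5 points (t, 5 df).

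**4. Chemoprevention on one period.** Halving the plan's numbers gives 4,000 v 9,350. Pooled rate = (58.5 + 84.15)/13,350 = 1.07%; null SE 0.194 points; alternative SE 0.213 points; power = Φ((0.5625 − 1.96 × 0.194)/0.213), about 80%. Splitting 4 v 3 instead of halving gives 8,000 × 4/7 = 4,571 v 18,700 × 3/7 = 8,014, and about 81%. Neither allows for clustering.

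**The case against.** The equivalence claim has much slack: 90% power survives a design effect up to about 7.2 at 50% attendance (normal reference). If site-period SD is near 1 point, the claim is true. This stands. A reader might infer that the claim of more than 90% power is false; the documents do not show that, because they give no site-period SD. It is unsupported, not refuted.

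A reader might also infer that intervals are several times too narrow for every core outcome. The size was worked out only for attendance and depends on the assumed SD. For rare outcomes binomial noise weighs more: at a 1% rate with an assumed site-period SD of 0.1 point, the SE ratio is only about 1.14.

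Three further readings go too far:
- That only period 1 is clean under carryover. The usual-care-first sites keep an uncontaminated second period.
- That a logistic model contradicts an absolute ±5% margin. A risk difference with its interval can be derived from the model.
- That aggregated control data prevent the analysis. The overall numbers promised are sufficient if supplied by site, period and screening type, and the planned comparisons imply that they will be.

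The 0.9% chemoprevention rate is offered as an upper case. With 4,000 v 9,350, power is about 97% at 0.7% and over 99.9% at 0.5%. But 0.9% is the figure on which the stated 90% rests.

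Finally, this is a feasibility study, and a variance estimator may be left to an analysis plan that is not shown. That excuses missing detail. It does not excuse a power calculation on the wrong unit, or an unconditional sentence that the design cannot support.

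**Conclusion.** The point holds in this form. Core-outcome power is calculated for independent women, and the stated analysis has no term for site-by-period variation, although the offer is assigned to seven non-randomised sites by period. Any such variation makes the intervals too narrow. For attendance at 50% the understatement is about 1.5-fold, 2.3-fold and 3.3-fold at SDs of 1, 2 and 3 points. The claim of more than 90% equivalence power for the pooled two-period comparison is conditional on SDs near 1 point.

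The sentence promising a valid and fully powered comparison whatever the heterogeneity or carryover is wrong. Under carryover neither remaining contrast is valid without further assumptions, and one period gives about 80% chemoprevention power on the plan's inputs even without clustering.

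Assumptions: the SDs are illustrative, cells are equal, sites vary independently, and the named logistic regression uses ordinary model-based standard errors.

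**What to change.** - Make the within-site crossover contrast primary for the core outcomes, with site and period effects and screening type.
- Take standard errors from the site-periods with a small-sample correction: at most 5 df, and fewer if sites move in blocks. If the four groups named under Setting are the units, 8 − 1 − 3 − 1 − 1 = 2 df remain.
- Report attendance as an absolute risk difference with 95% CI, set against ±5 points.
- Specify that counts in both groups are obtained by site, period and screening type.
- Treat the between-site, same-period contrast as supportive.
- Withdraw the validity and power sentence or state its conditions, and give power over a range of site-period SDs.

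The cost is analysis wording and a stratified data request. Intervals will be wider, and the power statement becomes conditional on how much sites drift between periods.

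### As printed, the second chemoprevention power condition (80% power at 10% uptake) is wrong; it is most probably a misprint of 1.0%, and the inputs behind both power figures need stating

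*Protocol article*

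**What the plan says.** The statement is in the protocol article, Analysis plan and power calculations, Core outcomes, in the paragraph on outcome 9. Of the 8000 women expected to consent, 1169 would be at sufficient risk to be considered for chemoprevention, and the article assumes that "10% of these would take it up". It concludes: "Thus 117 of the 8000 women (1.5%) receiving the intervention might be expected to be prescribed chemoprevention".

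For usual care it expects very few prescriptions among the 18,700 women sent the standard invitation. It then gives two power figures. Supposing a usual-care rate as high as 0.9%, it says: "we would have 90% power to detect this as significant at 5% level with two-sided testing, and 80% power if 10% took up chemoprevention".

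On group sizes, the same section says that 18,700 "women being offered BC-Predict should result in 8000 women taking it up". It also speaks of more than 8000 participants in each of the BC-Predict and NHSBSP groups. So two control group sizes are in play, 18,700 and something over 8000, and the power sentence does not say which was used.

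**The concern.** The two power figures form a pair: how much chemoprevention in usual care the comparison can tolerate before power falls to 90%, and then to 80%. By its grammar, the second condition continues the first and so refers to the usual-care rate. A usual-care rate of 10% would be almost seven times the rate expected under the intervention (10 / 1.4625 = 6.8), so the clause cannot describe a loss of power to 80%.

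The slip is less obvious than it might be, because 10% is a genuine parameter in the same paragraph, the uptake among eligible BC-Predict women. A reader may attach the 10% to that quantity instead. That does not work either, because one assumption would then carry two different powers.

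This is the only place where the article says how power for outcome 9 depends on usual-care uptake. The study is meant to inform a definitive evaluation, so the condition should be one that a reader can reproduce.

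**Working it through.** **Inputs, all from the Core outcomes section.** Two-sided 5% test. Intervention group n₁ = 8000, with p₁ = 117/8000 = 0.014625 (printed as 1.5%). Control rate p₂ = 0.9% for the first figure and, as printed, 10% for the second. Control n₂ = 8000 or 18,700.

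**Formula.** Normal approximation for two proportions with a pooled null variance:

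power = Φ[(|p₁ − p₂| − 1.96·SE₀) / SE₁],

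SE₀ = √[p̄(1 − p̄)(1/n₁ + 1/n₂)], with p̄ the average rate weighted by group size,

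SE₁ = √[p₁(1 − p₁)/n₁ + p₂(1 − p₂)/n₂].

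**Step 1: reproduce the 90%.** With 8000 per group, 117/8000 v 0.9%: the difference is 0.005625, p̄ = 0.0118125, SE₀ = 0.0017083 and SE₁ = 0.0017077. Then (0.005625 − 1.96 × 0.0017083)/0.0017077 = 1.333, so power = 90.9%. The first figure reproduces.

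**Step 2: the second figure as printed, on each literal reading of 10%.**

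- Usual-care rate of 10% v 117/8000, 8000 per group: the difference is 0.085375, SE₀ = 0.003675 and SE₁ = 0.003613. The standardised value is about 21.6, so power is about 100%, with usual care above the intervention. With 18,700 controls the result is the same.
- 10% uptake among the eligible BC-Predict women: 0.10 × 1169 ≈ 117, the base case of step 1. Power is about 91% with 8000 controls and about 97% with 18,700.
- 10% uptake across the whole intervention group v 0.9%: about 100%.
- 10% of eligible women taking it up in both groups: almost no difference is left, and power is about 4%.

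None gives 80%.

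**Step 3: read 10% as 1.0%.**

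| Intervention rate | Control n | Power at 0.9% | Power at 1.0% | Control rate for 90% | Control rate for 80% |
|---|---|---|---|---|---|
| 117/8000 | 8000 | 90.9% | 75.6% | 0.908% | 0.976% |
| 1.5% | 8000 | about 94% | 81.2% | 0.938% | 1.007% |
| 117/8000 | 18,700 | 97.4% | 88.7% | 0.990% | 1.051% |
| 1.5% | 18,700 | 98.5% | 92.4% | 1.021% | 1.083% |

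The first row fits the printed pair once the decimal point is restored. If the control rates were solved for 90% and 80% power, 0.908% and 0.976% round to 0.9% and 1.0%. The gap between 80% and the 75.6% at exactly 1.0% is then a rounding effect: power is steep here, falling about 4 points between 0.976% and 1.000%.

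**Step 4: the control group size.** With the 18,700 controls that the sentence names, both printed powers are below the computed ones at 0.9% and 1.0%. The printed pair therefore fits 8000 per group, which the sentence does not state.

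**The case against.** The strongest reply is that this is a plain misprint that misleads nobody. The paragraph expects very few usual-care prescriptions, treats 0.9% as an extreme and puts the intervention at 1.5%, so a 10% usual-care rate is visibly impossible. The step from 0.9% to 1.0% is the natural one, and with it both powers follow from a single set of inputs to the precision printed. No sample size, endpoint or analysis changes.

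Most of this stands. It rules out two stronger readings. A reader might infer that 80% cannot be obtained from the article's inputs at all; the 1.0% reading shows that it can, and that the intended sensitivity of power to usual-care uptake is about right. A reader might also infer from the 75.6% at exactly 1.0% that power is overstated. That figure rests on 8000 controls and on taking 1.0% as exact. With the 18,700 controls named in the sentence, power at 1.0% is 88.7%. For the same reason, the article should not simply be changed to claim about 76%.

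What the reply does not remove is that the condition is wrong as written, that 10% is also a real parameter of the same paragraph, and that the group size behind the pair is unstated.

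**Conclusion.** The clause is wrong as printed: no literal reading of 10% gives 80% power. It is most probably 1.0% with a lost decimal point. With 117/8000 and 8000 per group, 90% and 80% power correspond to control rates of about 0.91% and 0.98%, so the printed condition is about ten times too large.

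That the intended figure was 1.0% is an inference from the fit, not something that the article states. The calculation takes the article's 8000 consenting women and 117 prescriptions as given, with an unadjusted comparison of two proportions.

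The finding is limited to a misstated power condition and an unstated control group size. It does not show that the study is underpowered for outcome 9. On 18,700 controls, the powers at 0.9% and 1.0% are about 97% and 89%, and the stated values are conservative.

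**What to change.** Correct 10% to about 1.0%, and state in the same sentence the control group size and the intervention rate used, with both powers computed on those inputs. If 117/8000 and 8000 per group were used, the pair is 90% power at a usual-care rate of about 0.91% and 80% at about 0.98%. If the 18,700 controls were meant, 117/8000 gives about 97% at 0.9% and about 89% at 1.0%. The authors should confirm which was intended.

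The cost is one corrected clause and one added statement of inputs. The sample size and the analysis are unaffected.
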